### Multi-professional computer-assisted lifestyle intervention

The development of the GeMuKi intervention has been informed by experiences from the project 9 + 12 [34] and the GeliS study [28–30]. It aims to positively influence lifestyle-related risk factors of expecting mothers and their infants. The GeMuKi intervention is designed as a series of brief (approximately 10 min) counseling sessions performed by gynecologists, midwives and pediatricians during 11 prenatal and infant check-ups (see Fig. 2). The counseling sessions cover topics relevant during pregnancy and the infant’s first year relating to diet, physical activity, breastfeeding, and substance use. Figure 2 provides an overview of the topics addressed over the course of the GeMuKi lifestyle intervention. The topics are based on recently updated national recommendations developed by a multidisciplinary scientific task force [35, 36].

**Fig. 2 Fig2:**
[figure not shown]
Topics addressed by the GeMuKi intervention during routine prenatal visits and infant check-ups

Traditionally, behavioral interventions aiming at lifestyle changes rely on providing information and advice. This has proven to be less successful compared to approaches using elements of Motivational Interviewing (MI) to improve communication by health professionals [37, 38].

The GeMuKi intervention takes into consideration that communication of providers should be sensitive to expecting mothers’ health literacy in order to have a positive impact on behavior change. Therefore, multi-professional providers carrying out the GeMuKi intervention receive communication skills training. In addition to the content of the lifestyle intervention itself, the training covers MI techniques. MI is a client-centered counseling approach designed to enhance motivation for behavioral change by helping clients explore and resolve ambivalence [39].

A key element of MI used in the GeMuKi intervention is agenda mapping. Multi-professional providers employ agenda mapping to focus on a specific topic for lifestyle change (see Fig. 2). For this purpose, they use key message cards with pictograms developed by the Platform Nutrition and Physical Activity (peb) and experienced MI trainers.

After a participant has chosen a topic for lifestyle change, the provider continues the conversation using open-ended questions and then reacts to the participant’s answers using reflective listening techniques. Guided by the provider, participants set SMART (Specific Measurable Achievable Reasonable Time Bound) goals for lifestyle change, which can be accomplished until the next check-up visit.

Another objective of the GeMuKi intervention is to increase the level of cooperation between gynecologists, pediatricians and midwives. To achieve this, a novel telehealth platform was developed, which assists providers in the counseling process and enables them to communicate with each other.

#### Telehealth platform GeMuKi-Assist

The telehealth platform GeMuKi-Assist has the objective to facilitate cooperation between providers and enhance continuity of lifestyle counseling. It consists of the GeMuKi-Assist Counseling Tool, GeMuKi-Assist App, GeMuKi-Assist Study Monitor and the GeMuKi-Assist Server (see Fig. 3).

**Fig. 3 Fig3:**
[figure not shown]
Overview GeMuKi-Assist Telehealth platform

Providers and trained practice staff in both intervention and control regions use the GeMuKi-Assist Counseling Tool to enter data routinely documented in the maternity and child medical record booklets. In the intervention regions these data are used to create a GWG curve showing the development of GWG for each individual study participant in relation to the recommended range. The infants’ weight progression is displayed by means of percentile curves (see Additional file 1). Providers in the intervention regions also have access to key messages and guiding questions (i.e. standardized content) to support them in carrying out the GeMuKi intervention according to protocol and in alignment with MI techniques. They can also document goals for lifestyle change participants want to accomplish until the next check-up visit and have an option to enter notes regarding individual participants. To ensure continuity of the counseling, this information can be accessed by multi-professional providers involved in the counseling process. Individual goals for lifestyle change entered into the counseling tool are automatically send to the GeMuKi-Assist App as a reminder for study participants.

The GeMuKi-Assist App aims to support intervention group participants in performing lifestyle changes. It provides an overview of individual goals formulated during lifestyle counseling and sends automatic reminders for encouragement (push notifications). The App includes links to reliable sources of information (e.g. institutions providing health education) as well as services and supports available in the region (e.g. psychotherapists and dieticians). An option to conduct automated google keyword searches (e.g. lactation consultant and smoking cessation classes) is also included (see Additional file 1). In addition to these features, which are only available for participants in the intervention group, all participants can use the App for creating personal notes and completion of the electronic surveys in the study.

The GeMuKi-Assist Study Monitor supports the research process alongside the GeMuKi intervention. It is used to create user profiles for providers and study participants and for assigning study participants to corresponding multi-professional providers. Study coordinators also use the tool to monitor the data collection process. Automatic alerts from the GeMuKi-Assist server inform them for instance about incomplete data from study participant surveys and data entries in the counseling tool (see Additional file 1).

The GeMuKi-Assist Server handles and saves the data derived from the mobile App, the counseling tool and the study monitor in one central database. Access is controlled for different user groups, who must authorize themselves before accessing the data.

### Implementation strategy

To encourage uptake of the GeMuKi-intervention and implementation as planned an implementation strategy is being used consisting of the three elements: (1) a one-day training for gynecologists, midwives, pediatricians and practice assistants; (2) support by regional study coordinators in participating practices and (3) funding of novel tasks associated with the lifestyle intervention.

The one-day training is conducted before initiating the GeMuKi lifestyle intervention. It covers the basics of MI and the previously mentioned updated national recommendations for a health-promoting lifestyle during pregnancy and the infant’s first year. The training material includes a PowerPoint presentation, key message cards as well as brochures and stickers for the maternity and child medical record booklets. The presentation provides information on the purpose of the lifestyle intervention and key messages for a health-promoting lifestyle. It also summarizes the most relevant aspects of the evaluation study conducted alongside the intervention. In addition, the fundamentals of MI are introduced and the implementation of the GeMuKi intervention using selected MI elements explained. Knowledge of theoretical concepts are applied practically through role-play exercises and reinforced by videos with MI examples. The training also covers how to use the GeMuKi-Assist Counseling Tool. The training is carried out by experienced MI trainers from the Healthy Start-Young Family Network (Gesund ins Leben-Netzwerk Junge Familie). The training materials were developed based on the content of the curriculum of the Healthy Start-Young Family Network [40] and additional literature [41–43].

Regional study coordinators provide ongoing support to participating providers over the phone and during regular practice visits. They conduct a hands-on introduction to GeMuKi-Assist in the participating providers’ practices in both intervention and control regions and answer questions to help solve technical issues with GeMuKi-Assist and other local implementation challenges. They also provide information and advice to encourage protocol compliance (e.g. regarding weighing during pregnancy and flawless documentation). Furthermore, they perform data management. In case of missing data or data error, they contact the respective providers.

All providers participating in the study receive funding for implementing the GeMuKi intervention. They sign a contract with the participating health insurers and the Association of Statutory Health Insurance Physicians of Baden-Württemberg (KVBW). This contract forms the legal basis for the billing process. Providers in the intervention regions can bill 15 € per lifestyle counseling session. Providers in both the intervention and control regions can bill 5 € per documentation in GeMuKi Assist. Gynecologists and pediatricians in the intervention regions can receive up to 80 € and midwives up to 60 € per study participant when they carry out all counseling sessions in the study period (see Fig. 2).

### Data sources

Data will be collected at various points in time using multiple methods. Data sources include an electronic survey completed by study participants in the GeMuKi-Assist App at four points in time, data entered into the GeMuKi-Assist counseling tool during routine prenatal visits and infant check-ups, (focus group) interviews with multi-professional providers and intervention participants, statutory health insurance claims data and documents. At baseline, study participants also complete a short paper survey including demographic questions.

The selection of data sources was guided by the RE-AIM framework, which has been developed for evaluation of effectiveness and implementation of interventions in real-world settings [44, 45]. Table 1 provides a summary of constructs that will be measured for each dimension of the RE-AIM framework and data sources used.

**Table 1 Tab1:** Data sources and measured constructs aligned with RE-AIM dimensions

Dimension	Definition	Measured construct	Data source
Reach	The absolute number, proportion, and representativeness of individuals who are willing to participate in an initiative, intervention, or program.	Number and characteristics of participants and non-participants, reasons for non-participation	Administrative data in GeMuKi-Assist, focus groups with multi-professional providers, paper survey
Effectiveness	The impact of an intervention on important outcomes, including potential negative effects, quality of life, and economic outcomes.	Proportion of participants with excessive weight gain, infant body composition and weight development	Administrative data in GeMuKi-Assist
		Maternal lifestyle, knowledge, infant feeding, infant diet and physical activity	Electronic survey
Adoption	The absolute number, proportion, and representativeness of settings and intervention agents (people who deliver the program) who are willing to initiate a program.	Proportion and characteristics of participating multi-professional practices, reasons for non-participation and drop-out of practices	Administrative data in GeMuKi-Assist, documents and publicly available statistics
Implementation	*Setting level:* the intervention agents’ fidelity to the various elements of an intervention’s protocol, including consistency of delivery as intended and the time and cost of the intervention.	Implementation of brief lifestyle advice intervention (how and by whom?)	Focus groups with multi-professional providers,
		Intervention costs: human resources and time, health service use, implementation costs and training	Administrative data in GeMuKi-Assist, interviews with study participants, social health insurance claims data, documents
		Utilization of the GeMuKi Assist Counseling Tool, local adaptations of the intervention	Focus groups with multi-professional providers, interviews with study participants, administrative data in GeMuKi-Assist
	*Individual level*: the clients’ use of the intervention strategies.	Utilization of GeMuKi-Assist App, goal setting, links etc. Attainment of lifestyle change goals	Interviews with study participants, administrative data in GeMuKi-Assist
Maintenance	*Setting level:* the extent to which a program or policy becomes institutionalized or part of the routine organizational practices and policies.	Providers becoming experienced in delivering lifestyle advice, lifestyle advice becoming a routine component of practice processes	Focus groups with multi-professional providers, administrative data in GeMuKi-Assist
	*Individual level:* the long-term effects of a program on outcomes after 6+ months after the most recent intervention contact.	Maintenance of lifestyle changes and weight, drop out of study participants	Administrative data in GeMuKi-Assist, electronic survey

### Measures to assess effectiveness of the lifestyle intervention

Outcomes used to assess are described below. Table 2 provides a summary of the points of measurement and data collection methods.

**Table 2 Tab2:** Outcome measures at baseline and follow up

	Pregnancy				Infant’s first year					
	8–12 weeks	18–22 weeks	28–32 weeks	37–40 weeks	At birth	3–10 days	4–5 weeks	3–4 months	6–7 months	10–12 months
Maternal weight ^a^	x	x	x	x						x
Maternal physical activity	x			x				x		
Maternal smoking	x			x				x		x
Maternal alcohol use	x			x				x		x
Maternal diet	x			x				x		
Maternal knowledge	x			x				x		x
Breastfeeding ^a^							x	x	x	x
Infant weight and length ^a^					x	x	x	x	x	x
Infant nutrition										x
Infant physical activity								x		x

Notes: a = data are routinely collected and transferred into GeMuKi-Assist during check-up visits, all other measures are collected by an electronic self-report survey. Please note that this table only includes check-up visits, in which providers assess the specified outcomes

#### Maternal weight

During every prenatal visit maternal weight is routinely measured and documented in the maternity record booklet (see Table 2). GWG is calculated as the difference between self-reported pre-pregnancy weight documented during the first prenatal visit and weight at the last prenatal visit.

Excessive GWG is defined according to recommendations of the Health and Medicine Division of the National Academies of Science, Engineering and Medicine (previously known as Institute of Medicine, IOM). These recommendations differ depending on pre-pregnancy Body Mass Index (BMI). For underweight women (BMI < 18.5) the recommended weight gain ranges from 12.5 to 18 kg, for normal weight women (BMI = 18.5–24.9) from 11.5 and 16 kg, for overweight women (BMI = 25–29.9) from 7 to 11.5 kg and for obese women (BMI ≥ 30) from 5 to 9 kg [46]. Weight gain above the recommended range is classified as excessive GWG. This definition of excessive GWG is similar to the definition used in German guidelines, which currently recommend a maximum weight gain of 16 kg for normal weight women and a maximum of 10 kg for overweight and obese women [36]. To assess postnatal weight-retention, maternal weight data will also be collected 1 year after birth.

#### Maternal lifestyle behaviors

Physical activity behavior during pregnancy will be measured using the Pregnancy Physical Activity Questionnaire (PPAQ) [47]. Maternal smoking behavior and alcohol consumption will be measured using questions from the German Health Interview and Examination Survey for Children and Adolescents (KIGGS) [48]. Dietary behavior will be assessed with a modified version of the Food Frequency Questionnaire used in the German Health Examination Survey for Adults (DEGS), which measures frequency and portion size of the main food groups consumed over the past 4 weeks [49].

#### Maternal knowledge

To assess the ability of the lifestyle intervention to increase maternal knowledge of health promoting lifestyle aspects addressed during brief counseling, the research team developed specific knowledge questions. These questions are based on key messages included in the previously mentioned national recommendations for a health-promoting lifestyle during pregnancy and the infant’s first year [35, 36]. Data on study participants’ health literacy will be collected as part of a separate study component, which will be reported elsewhere.

#### Infant weight development and body composition

Infant weight and length will be routinely assessed during infant check-ups. Infant BMI will be calculated and compared with age-specific reference values. The German Kromeyer-Hauschild reference system [50] will be used, because national reference data are more suitable for diagnosis of childhood overweight and obesity [4, 51]. To allow for comparisons with international research, the research team will also compare infant weight and length measures with WHO Growth Standards [52].

#### Infant feeding, diet and physical activity

Breastfeeding will be routinely documented in the GeMuKi-Assist counseling tool during infant check-ups. At the age of 10 to 12 months study participants will complete a modified version of the food frequency questionnaire used in the German Health Interview and Examination Survey for Children and Adolescents (KIGGS) [53]. It measures frequency and portion sizes of main food groups infants consumed over the past 4 weeks. Additionally, parental feeding practices will be examined with single items from the Comprehensive Feeding Practices Questionnaire (CFPQ) [54]. Study participants will also complete several questions on their infants’ physical activity behavior developed by the research team.

### Evaluation of the implementation process

To gain insights into the implementation process, the study team will examine which components of the lifestyle intervention are implemented as planned and which components are being modified. For this purpose, focus groups and interviews with multi-professional providers and study participants will be carried out. Additionally, data entered into the GeMuKi-Assist Counseling Tool will be analyzed. Among other variables, the research team will analyze counseling contents, characteristics of participating providers, characteristics of expecting women and infants reached by the intervention and the total number of lifestyle counseling sessions provided. Finally, documents will be analyzed, such as minutes taken during implementation training.

Qualitative interviews and focus groups will provide insights into factors facilitating and hindering implementation from the perspective of providers and participants in the lifestyle counseling. These qualitative data will also shed light on contextual factors influencing the implementation process and outcomes for expecting mothers or their infants. To examine dynamic changes over time the research team will conduct interviews and focus groups both at the beginning and the end of the implementation process.

The evaluation of the implementation process will be informed by the Tailored Implementation for Chronic Diseases (TICD) checklist. This checklist is based on a synthesis of frameworks and taxonomies of determinants of professional practice [55]. It identifies determinants that influence professional practice in seven domains: guideline factors, individual health professional factors, patient factors, professional interactions, incentives and resources, capacity for organizational change, social political and legal factors. The checklist will guide the choice of measures used to understand factors influencing adoption, implementation and maintenance of the GeMuKi intervention by multi-professional providers.

### Economic evaluation

A cost-consequence analysis will be performed, because the GeMuKi intervention seeks to modify multiple outcomes in expecting mothers, their infants and at the system level. Cost-consequence analyses compare costs and consequences of alternatives in a disaggregated manner [56]. This provides greater transparency to decision makers, who want to weigh multiple aspects against each other [57, 58].

The analysis will be conducted from a health insurance perspective. Cost components considered in the analysis include intervention costs, health service use and implementation costs. Intervention and implementation costs will be calculated based on documentation of personnel time and other resources used. Service use will be calculated using social health insurance claims data. These data include in- and outpatient treatment, medication use, aids and remedies, use of preventive services and sick leave periods. Outcomes considered in the analysis will include the above described lifestyle-related risk factors for overweight and obesity in expecting mothers and their infants. Additionally, outcomes at the system-level will be considered, such as changes in collaboration practices between multi-professional providers. These will be derived from qualitative data analyses conducted to gain understanding of implementation processes.

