Does the GeMuKi intervention effectively improve lifestyle-related risk factors for overweight and obesity in expecting mothers and their infants compared to routine practice?How does implementation of the GeMuKi intervention take place in practice? What factors facilitate or hinder successful implementation during routine prenatal visits and infant check-ups?What costs, health service use and consequences are associated with the GeMuKi intervention from a public payer perspective? How do these compare to routine health practice?

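### The economic evaluation takes the health insurer's perspective but costs the intervention from personnel time and resources, not from the fees the insurers contracted to pay

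*Protocol article*

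**What the plan says.** The third research question in the Introduction asks: "What costs, health service use and consequences are associated with the GeMuKi intervention from a public payer perspective", and how these compare with routine practice. The Economic evaluation section repeats the viewpoint: "The analysis will be conducted from a health insurance perspective".

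The same section fixes how the cost components are obtained. For the intervention and its roll-out: "Intervention and implementation costs will be calculated based on documentation of personnel time and other resources used". For the rest: "Service use will be calculated using social health insurance claims data". Table 1, under Data sources, likewise describes intervention costs in terms of human resources and time. It does so in one row that also covers health service use, implementation costs and training.

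The price of the intervention to the insurers is in the Implementation strategy section. Providers bill under a contract with the participating insurers and the regional physicians' association: "Providers in the intervention regions can bill 15 € per lifestyle counseling session", and "Providers in both the intervention and control regions can bill 5 € per documentation in GeMuKi Assist". The ceiling is also given: "Gynecologists and pediatricians in the intervention regions can receive up to 80 € and midwives up to 60 € per study participant". The Economic evaluation section does not mention these fees.

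**The concern.** The perspective of an economic evaluation determines what counts as a cost. When a service is billed at an agreed fee, the insurer's cost is the fee. The minutes that the service takes are a cost to whoever delivers it. A payer perspective combined with a time-and-resource costing rule means that, followed literally, the delivery cost describes resource use rather than insurer outlay.

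The Discussion says that the funding scheme could be scaled up and that the study is to inform the federal decision on roll-out and public funding. The fee schedule is the cost which that decision maker would face. If delivery is costed in another way, the third research question is not answered from its own perspective. A related question is how the documentation fee, which practices in both arms can bill, enters the comparison with routine care.

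**Working it through.** **Inputs from the protocol article**
- Counseling fee 15 €, intervention regions; documentation fee 5 €, both arms (Implementation strategy).
- Maximum per participant: gynecologist 80 €, pediatrician 80 €, midwife 60 € (Implementation strategy).
- 11 check-ups with sessions of about 10 minutes (Multi-professional computer-assisted lifestyle intervention).

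**Assumption.** The article gives no hourly personnel cost; 30 to 150 € per hour is assumed to show the range.

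**Step 1: reproduce the stated maxima.** Fee per documented session = 15 + 5 = 20 €. Implied sessions: 80/20 = 4, 80/20 = 4 and 60/20 = 3. Their sum is 11, which matches the 11 check-ups. With the counseling fee alone, 80/15 = 5.33 is not a whole number, so the maxima include the documentation fee.

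**Step 2: insurer cost at full delivery.**
- Total: 11 x 20 = 220 € per intervention participant.
- Counseling: 11 x 15 = 165 €.
- Documentation: 11 x 5 = 55 €.

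**Step 3: time-based cost of the same counseling.** Time = 11 x 10 = 110 minutes. Cost = (110/60) x hourly rate. The like-for-like comparator is the 165 € counseling fee, because no documentation time is counted here.

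| Assumed rate (€/h) | Time-based cost (€) | Minus 165 € | Ratio to 165 € |
|---|---|---|---|
| 30 | 55 | -110 | 0.33 |
| 60 | 110 | -55 | 0.67 |
| 90 | 165 | 0 | 1.00 |
| 120 | 220 | +55 | 1.33 |
| 150 | 275 | +110 | 1.67 |

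The two methods agree only at 15 € per 10 minutes, which is 90 € per hour.

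**Step 4: fee increment between arms**, if all 11 check-ups are documented in both arms.
- Documentation fee counted in both arms: 220 - 55 = 165 €.
- Documentation fee removed from both arms: 165 - 0 = 165 €.
- Documentation treated as intervention cost in one arm and as study cost in the other: 220 - 0 = 220 €.

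**The case against.** The costing sentence says neither that the time is the providers' nor that fees are excluded. It covers intervention and implementation costs together, and the work of trainers and regional coordinators fits its wording and has no listed fee. It names quantities, not unit prices, so sessions could still be valued at the contract fee. Table 1 lists administrative and claims data among the sources for its combined cost row. A journal article may leave unit valuation to a fuller plan. A cost-consequence analysis also reports components separately, so a reader could partly rebuild the insurer's cost.

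Much of this stands. That the time is the providers' is an inference, time-based costing suits training and coordination, and fee-based costing may be feasible from the planned data. But the article does not leave the costing basis open. It states a perspective and a method, and nothing in it says that sessions will be valued at the fee.

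A reader might infer more than the article supports:
- **That sessions will be counted twice.** This happens only if the contract fees also appear in the claims data, which the article does not say.
- **That the control arm's documentation fees make the increment 25% too small** (55/220). This presumes that documentation is an intervention cost in one arm and a study cost in the other. The article does not settle that. Under Telehealth platform GeMuKi-Assist, data entry takes place in both arms, and in the intervention arm it also feeds the weight-gain curve. Nor does the article say that these fees will be treated as usual care.
- **That the 20 € enrolment allowance distorts the comparison.** Recruitment procedure grants it per enrolled participant without distinction of arm and does not name its payer. It cancels in the difference.
- **That time-based costing understates the insurer's cost.** The direction depends on an hourly rate that the article does not give. Setting 110 minutes of counseling against the full 220 € would also not be like for like.

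**Conclusion.** The concern holds as a mismatch between the stated perspective and the stated costing basis. Under the costing rule as written, delivery cost would reflect resources used rather than the insurer's outlay. At an assumed 30 to 150 € per hour, the counseling component could fall between 110 € below and 110 € above the 165 € counseling fee per participant. The sign is unknown, and the gap is zero at 90 € per hour.

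These figures assume that all 11 sessions are delivered at 10 minutes each and that the time counted is session time. With fewer sessions, both costs fall. The fee increment between arms is 165 € or up to 220 €, according to how documentation is classified, and neither value can be called wrong from the article alone. The primary outcome, sample size and effectiveness analyses are untouched. The point merits a change because it decides whether the third research question is answered from the perspective in which it is asked.

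**What to change.** In the Economic evaluation section:

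1. For the payer analysis, value counseling and documentation at the contracted fees (15 € and 5 €) times the number of sessions and documentations billed.
2. Report personnel time for delivering sessions separately, as provider resource use. Keep time-based costing for training and coordinator support.
3. State whether contract fees appear in the claims data and, if so, count them once.
4. Show the 5 € documentation fee as its own line in both arms, and give the increment with and without it (up to 220 €, or 165 €), saying which classification each rests on.
5. No adjustment of the arm difference is needed for the enrolment allowance.

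The cost is a few sentences in the economic analysis plan. The evaluators need session or billing counts. The article does not show that they hold the billing data, but Evaluation of the implementation process already plans to analyze the total number of counseling sessions provided. Counts of documentation entries in both arms are needed as well.
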